### **Definition of the study population**

Patients will be identified from CPRD, both GOLD and Aurum databases will be used as the primary care data source

## Selection of comparison groups/controls

For the second phase of this study, we aim to compare the clinical outcomes of patients with NVAf prescribed OACs and who were not prescribed OACs. This will be done by including incident cases of NVAf identified from phase one cohort from 2009 to 2019 and further divide them into two groups; cases are patients treated with OACs within one year of NVAf diagnosis and controls are those who did not receive OACs for  $\geq 1$  year after NVAf diagnosis. Many confounders will be controlled for when evaluating the effect of treatment (OACs) on the clinical outcomes of interest (i.e. stroke, bleeding, or all-cause mortality). Potential confounders are likely to include patient age, sex, and presence of hypertension, diabetes, coronary artery disease, heart failure, kidney disease, liver disease, peripheral artery disease, fall risk, history of stroke or bleeding, malignancy, anaemia, alcohol abuse, antiplatelet use or non-steroidal anti-inflammatory drugs. At first, we aim to perform propensity score matching method using a multivariable logistic regression model that contains the confounders mentioned above to estimate patient's probability to receive OACs. Matching will operate by taking each case and finds the closest propensity score match among controls, within a predetermined caliper bandwidth. However, in case if the matching method failed to achieve balance among the two patient groups or caused substantial exclusion of individuals from the main cohort, then we will consider overlap propensity score weighting. By applying overlap propensity score weighting each patient's will be weight by the probability of that patient being assigned to the opposite treatment group.

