### Specific aims:

1. To determine the incidence of NVAF diagnosis in England from the year 2009 to 2019.
2. To determine the proportions of patients with NVAF and those with NVAF and cancer who were prescribed OACs, antiplatelet alone or no treatment.
3. To examine the temporal trends of prescribing different types of OACs (i.e. VKAs and NOACs), and assess the factors associated with not prescribing OACs including patient demographics, socioeconomic status, history of cancer and other comorbidities, stroke and bleeding risk.
4. To assess the effect of OACs prescribing vs. no OACs on the clinical outcomes (stroke, bleeding, and death) in a comparative cohort of NVAF patients eligible for anticoagulation after controlling for patients' comorbid conditions, frailty, age, and antiplatelets use.
5. To assess the rate of clinical outcomes (i.e. bleeding recurrence, stroke, and mortality) after MB events and how they relate to OACs resumption and the timing of restarting OACs after the MB event.
6. To explore the variability across patient groups regarding OACs resumption after MB events and whether patients have continued on the same OAC before the MB event, switched to another OACs or received lone antiplatelet therapy.
7. To assess and compare patients' risk for stroke and bleeding recurrence using HAS-BLED, CHA2DS2-VASC, HEMORR?HAGES and GARFIELD-AF risk assessment scores, at the time of the indexed major bleeding event.

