### Rationale:

Achieving these specific aims will allow the identification of predictors for the under prescription of OACs in NVAF who are eligible for anticoagulation therapy. By further comparing the clinical outcomes between OACs treated and not treated individuals we will be able to determine the characteristics of patients who are still more likely to benefit from receiving anticoagulation therapy. The outcomes of restarting OACs after major bleeding events and their associated benefits or risks are still not well known and the proper timing of restarting OACs after major bleeding events is still not certain and further studies are needed to evaluate the effect of different time intervals to resume OACs. Moreover, available risk assessment scores such as the HAS-BLED, CHA2DS2-VASC, and HEMORR?HAGES are used to assess patients' risk for stroke and bleeding when initiating OACs, but it is unclear if these scores or the new GARFIELD-AF score could be used to inform decision-making for restarting OACs after major bleeding events.

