### **Feasibility counts**

Earlier reports on AF prevalence in England estimated that 2.5% of the population have AF for both valvular and non-valvular AF (NVAf), with increasing prevalence in older age-groups. A previous study, that used CPRD GOLD to identify incident cases of NVAf, identified around 91,000 cases from 2001 to 2013. We conducted a simple feasibility count for incident cases of NVAf patients in CPRD GOLD, and we identified at least 120,000 incident cases are expected for the period (2009-2019) with an annual average of around 11,000 new cases. According to a previous study in the UK that estimated the proportion of AF patients at risk for stroke but did not receive either OACs or antiplatelets to be around 12% of total AF cases. Therefore, we expect to identify around 14,000 NVAf patients not treated with OACs across the duration of the study

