**Covariates:**

- Patients' demographic information (age, gender, ethnicity, body mass index (BMI), geographic location (rural vs. urban), smoking status, alcohol consumption, Charlson comorbidity index for the severity of comorbidity (Appendix 4), electronic frailty index (eFI), and the index of multiple deprivation (IMD).
- For the sub-group of patients with NVAf and history of cancer, cancer diagnosis will be assessed at the index date of NVAf diagnosis and classified by cancer type into breast, prostate, colorectal, haematological, lung, and other types, and by cancer metastasis status.
- Drugs that affect either stroke or bleeding, or commonly interact with OACs, such as antihypertensive drugs, statins, antiarrhythmics, antidiabetic drugs, anticonvulsants, non-steroidal

anti-inflammatory drugs, corticosteroids, systemic azoles, HIV protease inhibitors and ciclosporin. (Appendix 2).

- The CHA2DS2-VASc stroke risk score that consists of 9 points, one for each of: congestive heart failure (CHF), hypertension (HTN), age  $\geq 75$  years (x 2 points), diabetes mellitus (DM), prior stroke or transient ischemic attack (TIA) or thromboembolism (x 2 points), vascular disease, age 65 to 74 years, and sex category. Information included in the CHA2DS2-VASc score will be identified using Read codes (Appendix 3 and 4), except for age and sex, to build the score and assess the risk of stroke for all included patients in the cohort. Further categorization of eligibility for OACs will be carried according to individual CHA2DS2-VASc scores; “not eligible for OAC” if CHA2DS2-VASc score = 0 in males, or 1 in females; and “OAC eligible” if CHA2DS2-VASc score  $\geq 1$  in males, or  $\geq 2$  in females.

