## 2. Phase 2 - Comparative study

**Exposures:** In this cohort, prescriptions for OAC will determine patient’s exposure status. NVAf patients identified from phase one and who have received a continuous prescription of either VKAs or NOACs within one year of NVAf diagnosis will be in the OACs “exposed group”. While “OACs unexposed” patients are individuals in phase one who haven’t received a prescription for anticoagulation therapy and remained OACs free for  $\geq 1$  year from NVAf diagnosis.

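### Aim 4 concerns NVAF patients eligible for anticoagulation, but the Phase 2 selection and exposure rules apply no eligibility criterion, so the hazard ratios would describe a broader population

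*Protocol*

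**What the plan says.** The protocol describes the intended population in two places. Specific aim 4 places the comparison "in a comparative cohort of NVAF patients eligible for anticoagulation". The Rationale speaks of "predictors for the under prescription of OACs in NVAF who are eligible for anticoagulation therapy".

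The rules that form the groups are elsewhere. Under Selection of comparison groups/controls: "This will be done by including incident cases of NVAf identified from phase one cohort from 2009 to 2019". Treated patients are those given an OAC within one year of diagnosis, and "controls are those who did not receive OACs for" at least one year after it. The Phase 2 exposure definition says the same of the unexposed: these "patients are individuals in phase one who haven’t received a prescription for anticoagulation therapy and remained OACs free" for at least a year. Neither place mentions stroke risk or eligibility as a condition of entry.

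The plan does have an eligibility variable. The Phase 1 covariates state: "Further categorization of eligibility for OACs will be carried according to individual CHA2DS2-VASc scores". A patient is not eligible "if CHA2DS2-VASc score = 0 in males, or 1 in females", and eligible at higher scores. The Phase 1 analysis text uses this to describe the prescribed and not-prescribed groups and to stratify yearly trends. The Phase 2 analysis text does not use it.

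**The concern.** The aim and the cohort definition describe different populations. An analyst working from the selection and exposure sections would keep patients whom the protocol itself classes as not eligible, treated and untreated alike. An analyst working from Aim 4 would remove them. Both could claim to follow the protocol, and they would report hazard ratios for different target populations.

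What is at stake is interpretation. The stated objective is to evaluate the clinical outcomes of under-prescription. A result that includes patients outside the plan's own eligible category does not answer that question cleanly, and a reader could not tell how much of the estimate came from them. Phase 3 is drawn from the Phase 2 treated group, so it takes on whichever population is used.

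**Working it through.** **1. The passages side by side**

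| Place in the protocol | Population or use |
|---|---|
| Specific aim 4; Rationale | NVAF patients eligible for anticoagulation |
| Selection of comparison groups; Phase 2 exposures | Incident Phase 1 cases, split by OAC receipt only |
| Technical Summary; Phase 2 analysis | No eligibility restriction added |
| Phase 1 covariates | Eligible and not-eligible categories defined |
| Phase 1 analysis | Categories used for description and for stratifying trends |
| Phase 2 covariates; Plan for addressing confounding | Stroke risk as covariate and Cox adjustment, not as entry criterion |

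**2. Does matching restore the Aim 4 population?** The propensity model includes age, sex, hypertension, diabetes, heart failure, coronary and peripheral artery disease and stroke history, which are most of the score's components. A low-risk control is therefore paired with a low-risk treated patient or dropped by the caliper. That balances the groups. It does not remove low-risk pairs. The fallback, overlap weighting, does not exclude by eligibility either.

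**3. Illustration of size.** The documents give neither the ineligible share f nor the stroke rate p0 in such patients. Assume f = 5% to 40%, p0 = 0.2% to 1.0% per year, and no OAC effect in them. Assume also that the yearly rates under Sample size considerations (8% without OAC, 2.8% on warfarin) hold for eligible patients.

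With f equal in both groups, as matching would aim for:
- unexposed rate pU = 0.08(1 − f) + p0·f
- exposed rate pE = 0.028(1 − f) + p0·f
- RR = pU/pE; risk difference = 0.052(1 − f)

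| f | p0 | pU | pE | RR | Risk difference |
|---|---|---|---|---|---|
| 0 | – | 8.00% | 2.80% | 2.86 | 5.2 points |
| 5% | 0.2% | 7.61% | 2.67% | 2.85 | 4.9 points |
| 5% | 1.0% | 7.65% | 2.71% | 2.82 | 4.9 points |
| 40% | 0.2% | 4.88% | 1.76% | 2.77 | 3.1 points |
| 40% | 1.0% | 5.20% | 2.08% | 2.50 | 3.1 points |

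If ineligible patients sat only in the unexposed group, as in a crude unmatched comparison, RR = pU/0.028. This runs from 0.0765/0.028 = 2.73 down to 0.0488/0.028 = 1.74. Matching is meant to prevent that case.

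**4. Power and the cost of restricting.** The protocol states 194 unexposed and 970 exposed. The standard two-proportion formula (two-sided 0.05, 80% power, ratio k = 5, pooled rate p̄ = (p1 + k·p2)/(1 + k)) is

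n = [1.96·√(p̄(1 − p̄)(1 + 1/k)) + 0.842·√(p1(1 − p1) + p2(1 − p2)/k)]² / (p1 − p2)².

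With 8% in the unexposed and 2.8% in the exposed it gives 152 unexposed. The stated 194 appears only if the two rates are swapped between the groups (194.4). With the groups as labelled, 194 + 970 gives 87% power, so the stated figure is conservative. That mismatch is a separate matter.

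Under the balanced scenarios above the required unexposed number rises from 152 to between 161 and 296. With 14,000 unexposed and full 5:1 matching, power stays near 100%.

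Restricting to eligible patients leaves 14,000 × 0.95 = 13,300 at f = 5%, or 14,000 × 0.60 = 8,400 at f = 40%. And 8,400/194 = 43 times the stated need.

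**The case against.** The strongest reply is that this is silence rather than contradiction. Aim 4 names the eligible cohort, the Phase 1 covariates supply the cut-off, and the selection text does not say that all cases are taken. Read together, the restriction might be implied. The section defining the study population is a single line and may have been cut when the text was read from the PDF. These points make the defect a gap between passages, but they do not close it. The selection and exposure sections are full statements of both groups and neither contains the condition.

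A second reply is that the effect is small. That largely stands: after balanced matching the ratio moves little in the illustration unless the ineligible share is large, and power is unaffected.

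A third is that rewording Aim 4 and reporting results by eligibility would reconcile the text equally well. That is a legitimate alternative. Restriction is preferred here because both the aim and the rationale name eligible patients.

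Three stronger readings are tempting but unsupported:
- A reader might infer that ineligible patients make up a large part of the unexposed group and sharply lower its stroke rate. No ineligible share is given. The feasibility figure cannot serve as a base either: it comes from a study that "estimated the proportion of AF patients at risk for stroke but did not receive either OACs or antiplatelets to be around 12"%, whereas the plan's not-prescribed group also includes patients on antiplatelets alone. Caliper matching would further limit how many ineligible controls remain.
- A reader might take the feasibility count as proof that Phase 2 was meant to be restricted. The borrowed percentage concerns patients at risk of stroke, but the section ends by counting untreated NVAF patients in general.
- A reader might say that the plan's absolute-benefit estimates are weakened. Phase 2 plans hazard ratios, and no absolute-benefit analysis is described.

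**Conclusion.** The inconsistency is real. Aim 4 and the Rationale concern eligible patients; the Phase 2 selection and exposure rules admit patients whom the plan classes as not eligible, in both groups. The consequence is a broader target population than the aim states, not a demonstrated bias and not a loss of power.

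Its size cannot be derived from the documents. Under the assumed ranges and balanced matching, a one-year stroke risk ratio of 2.86 would become something between 2.85 and 2.50. The 2.50 end needs 40% ineligible patients with a 1.0% yearly stroke rate and no OAC effect. These figures show scale only; the planned measure is a hazard ratio, over a composite wider than stroke.

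The point is about which patients the analysis describes. It takes no position on who should be treated.

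**What to change.** Reconcile the passages. In both Selection of comparison groups/controls and the Phase 2 exposure definition, state that the primary Phase 2 analysis is restricted to patients in the OAC-eligible category at NVAF diagnosis, as already defined in the Phase 1 covariates. Report the all-NVAF result as a sensitivity analysis.

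Say in the same place whether Phase 3 is drawn from the restricted or the full treated group, because Aims 5 to 7 carry no eligibility condition.

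The cost is small. The score is already to be computed for every patient at the index date. Some patients are lost from the primary analysis, but on the assumed range about 8,400 to 13,300 unexposed patients remain, far above the stated 194.

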## Study background

In 2017, it was estimated that 1.4 million people in England have atrial fibrillation (AF), which is equal to 2.5% of the population. One of the main therapeutic goals in AF is to reduce the risk of thrombo-embolism and stroke, which can be achieved by using oral anticoagulants (OACs). Previous observational studies in the UK that used primary care data such as the CPRD, have found a steady increase in the prescribing of OACs throughout the past decade. This observed increase in OACs prescribing was further explained by the introduction and adoption of non-vitamin K oral anticoagulants (NOACs). This increasing uptake of OACs also corresponds to a change in the European Society of Cardiology (ESC) guidelines that recommended the treatment of moderate-risk to high risk AF patients with OACs rather than antiplatelets, as well as a change in the Quality and Outcome Framework (QOF) to incentivize prescribing of anticoagulants. However, despite this encouraging increase in OACs initiation in AF patients, evidence from an observational study using CPRD have showed that the proportion of patients not receiving any anticoagulation therapy from the year 2012 to 2016 remained the same, at around 15% of patients with non-valvular atrial fibrillation (NVAF).

The decision to start OAC therapy in AF patients mainly depends on balancing patient's risk for ischemic strokes against their risk for bleeding. Current guidelines recommend estimating stroke

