### **Study design**

The first phase of this study will be a large population-based cohort study to identify incident cases of NVAf between January 1st, 2009 and 30th of June 2019; to determine the proportions of NVAf patients who have received a prescription for OACs or no treatment; to examine predictors of OACs prescribing. Given the described study aims and objectives, this study design will allow for a longitudinal analysis of incident NVAf cases and the subsequent timing of OACs prescribing with no comparator groups.

The second phase will be a comparative cohort study that aims to compare the clinical outcomes of NVAf based on their exposure status to anticoagulation therapy. Both patient groups will be identified from phase one and further divided into comparative groups of patients who have been prescribed OACs and patients with no anticoagulation therapy. The comparison will be undertaken after controlling for factors that could influence a patient's exposure to OACs and the outcomes to be explored, more details provided in section M.

Finally, the third phase of this study will be a separate analysis of the treatment group from phase two who have experienced major bleeding events. This study design is suitable for this phase as it will allow for a longitudinal analysis of NVAf patients from the indexed bleeding events and onward to evaluate the clinical outcomes (i.e. stroke, bleeding reoccurrence and mortality) related to OACs resumption or not and the timing of restarting OACs after the bleeding event, it will also allow for post-haemorrhage assessment of stroke and bleeding risk using different risk scores, and the identification of predictors for not resuming anticoagulation therapy.

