2. Phase 2 – Comparative study: For comparison of demographic variables and comorbidities among OACs treated and not treated individuals, independent sample t tests will be used for numeric variables, while Chi squared  $\chi^2$  tests or Fisher exact tests will be used for categorical variables. To control for imbalances in patient characteristics between cohorts, we will calculate an exposure-specific propensity score as the predicted probability of receiving OACs conditional upon individuals baseline covariate (as described in section M) using logistic regression models. Then we will consider applying propensity score matching methods to match each OACs unexposed controls to up to 5 NVAF OACs exposed cases using a calliper of 0.2 standard deviation (SD) of the propensity score logit. After matching, Cox regression will be used to compute hazard ratios (HRs) of the outcomes of interest, comparing exposure to OACs versus no OACs. Initially crude HRs will be obtained, then stratified by type of OACs (i.e., VKAs and NOACs) and adjusted for age, and other important covariates described in section N. In this phase immortal time bias would occur due to the definition of exposure, where in the time from AF diagnosis till receipt of OACs those in the “OACs prescribed group” cannot have the outcome by design, otherwise they would have been classified as non OAC users. To avoid the problem of immortal time bias, we will consider using time-varying exposures, where in a survival analysis, the time period previous to the index date of OACs initiation is reclassified as nonuser for those in the “OACs prescribed group”.

3. Phase 3 – Major bleeding events cohort: At first, we will use descriptive statistics to present the overall characteristics of this cohort who have experienced major bleeding events while taking OACs. After that patients will be divided to 2 groups one for the patients who resumed anticoagulation after the index major bleeding event and the other for the group who remained OACs free and will compare the patient characteristics between the two groups using Chi squared  $\chi^2$  tests, Fisher's exact tests, and analysis of variance, as appropriate. Survival (time-to-event) models will be constructed to compare the time between the indexed major bleeding to the earliest event of stroke, bleeding, or all-cause mortality considering if patients were restarted on OACs or not. In Cox models we will control for age, time to OACs resumption, CHA2DS2-VASc

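### Phase 2 pools NVAF diagnoses from 2009 to 2019 but leaves calendar year of diagnosis out of the matching and adjustment, which matters most for the NOAC hazard ratio

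*Protocol*

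**What the plan says.** Phase 2 takes its patients from Phase 1, "including incident cases of NVAf identified from phase one cohort from 2009 to 2019 and further divide them into two groups": OAC within one year of diagnosis, or OAC-free for at least one year (Protocol, Selection of comparison groups/controls). The only calendar limits are those for case identification, "between January 1st, 2009 and 30th of June 2019" (Study design).

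The same section on comparison groups lists the confounders: "Potential confounders are likely to include patient age, sex, and presence of hypertension, diabetes, coronary artery disease, heart failure, kidney disease", followed by further comorbidities, fall risk, stroke and bleeding history, and antiplatelet or NSAID use. The propensity score then comes from "a multivariable logistic regression model that contains the confounders mentioned above". Diagnosis year is not on the list.

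Data/statistical analysis (Phase 2) matches up to five exposed patients to each unexposed patient "using a calliper of 0.2 standard deviation (SD) of the propensity score logit", with no exact match on year. For the outcome model it says "Initially crude HRs will be obtained, then stratified by type of OACs (i.e., VKAs and NOACs" and then adds covariate adjustment. Neither the Phase 2 covariates (Exposures, outcomes and covariates) nor the Cox adjustment set (Plan for addressing confounding) contains calendar year.

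The Study background reports that earlier UK studies "have found a steady increase in the prescribing of OACs throughout the past decade". It attributes the rise to NOAC adoption and links it to changes in the ESC guideline and in QOF incentives. It also reports that the share of NVAF patients without any anticoagulation stayed at around 15% from 2012 to 2016.

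**The concern.** By the Protocol's own account, the chance of receiving an OAC, and which one, depended on when the patient was diagnosed. If stroke, bleeding or death rates, or the way they are coded, also changed between 2009 and 2019, diagnosis year confounds the comparison. Two patients with the same comorbidities and medication but diagnosed ten years apart get the same propensity score, so matching treats them as equivalent.

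No other planned step repairs this:

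- The fallback, overlap weighting, balances only what the score contains.
- The time-varying exposure deals with immortal time.
- The E-value addresses unmeasured confounders, and diagnosis year is measured.

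The NOAC stratum is most exposed. Nothing stops NOAC users from being compared with untreated patients diagnosed before NOACs were in use. Phase 2 is declared hypothesis testing (Study type), and the VKA and NOAC hazard ratios could be distorted by different amounts.

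**Working it through.** **Where diagnosis year could enter Phase 2**

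| Place in the Protocol | Diagnosis year included? |
|---|---|
| Confounder list for the score (Selection of comparison groups/controls) | No |
| Phase 2 covariates (Exposures, outcomes and covariates) | No |
| Matching rule (Data/statistical analysis) | No; score and caliper only |
| Cox adjustment (Plan for addressing confounding) | No |
| Period restriction on the unexposed group, overall or by OAC type | None |

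Phase 1 analyses OAC trends by year, so the variable is available.

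**Size.** The Protocol has no figure to reproduce here, because it gives neither yearly exposure shares nor an event-rate trend. What follows is illustration. Assumptions: equal numbers of diagnoses per year, a linear change in the untreated share, event rates falling 3% to 5% a year (factor r = 0.97 to 0.95), and no true OAC effect. The apparent HR is then about r^g, where g is the gap in mean diagnosis date in years (exposed minus unexposed).

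*All OACs, untreated share falling from 40% to 15% over the 10.5-year window.* p(t) = 0.40 − 0.25t/10.5.

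- Untreated: ∫p dt = 10.5 × 0.275 = 2.89 and ∫t·p dt = 22.05 − 9.19 = 12.86, so the mean is 12.86/2.89 = 4.45 years.
- Treated: ∫(1 − p) dt = 10.5 − 2.89 = 7.61 and ∫t(1 − p) dt = 55.13 − 12.86 = 42.26, so the mean is 42.26/7.61 = 5.55 years.
- g = 1.1 years; 0.97^1.1 = 0.97 and 0.95^1.1 = 0.95.

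*All OACs, other assumed trends* (whole calendar years, 2019 at half weight):

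| Untreated share, 2009 to 2019 | g (years) | Apparent null HR (3% to 5% fall a year) |
|---|---|---|
| flat at 15% | 0.0 | 1.00 |
| 30% to 15% | 0.8 | 0.98 to 0.96 |
| 45% to 20% | 1.0 | 0.97 to 0.95 |
| 50% to 15% | 1.5 | 0.96 to 0.93 |
| 60% to 10% | 2.0 | 0.94 to 0.90 |

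*NOAC stratum.* Further assumption: diagnosis dates of NOAC starters spread evenly from 2013 to mid-2019, that is t = 4 to 10.5, mean 7.25.

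- Flat untreated share (mean 10.5/2 = 5.25): g = 2.0; 0.97^2.0 = 0.94 and 0.95^2.0 = 0.90.
- Share falling from 40% to 15% (mean 4.45): g = 2.8; 0.97^2.8 = 0.92 and 0.95^2.8 = 0.87.

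A flat untreated share therefore removes the gap for all OACs together but leaves about 2 years in the NOAC stratum. If event rates or their recording rose over time, the bias would run the other way.

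**The case against.** The Study background's flat figure of about 15% for 2012 to 2016 is real counter-evidence. If it held over the whole window, the overall comparison would have no calendar gap. That stands as a limit on size. It covers only part of the window, however, and the Phase 1 definition of not being prescribed an OAC also takes in lone antiplatelet users, whose share may have fallen as guidance moved towards OACs. Having antiplatelet use in the score may absorb some of that trend, but not the year itself.

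The confounder list is introduced as likely rather than final, and a statistical analysis plan could extend it. But the next sentence builds the score from the variables listed, and the later covariate and adjustment lists omit year too.

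The main stroke result is also unlikely to turn on this. The sample size section plans for a relative risk of 2.8, an HR near 1/2.8 = 0.36, against which a distortion of 3% to 5% is small. This is correct for stroke, but the Protocol gives no planned effect for bleeding, mortality or the OAC-type strata.

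Stronger readings are tempting, and the text does not support them:

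- **Early untreated patients against late, mainly NOAC, patients.** The plan permits matches across years but does not separate the groups by period. VKAs are included throughout and no VKA/NOAC split is given.
- **Patients diagnosed in the last year can enter only the exposed group.** This follows only if observation closes on 30 June 2019. The Protocol gives that date for identifying cases and states no end of follow-up. Nor would all of the roughly 11,000 cases a year (Feasibility counts) be affected. Only untreated patients could lose eligibility: 11,000 × 12% = 1,320 to 11,000 × 15% = 1,650, using the untreated shares quoted in the Protocol.

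**Conclusion.** The point holds as an omission. Diagnosis year is a measured, plausible confounder by the Protocol's own account, and it enters neither the score, the matching nor the outcome model. Over-representation of untreated patients in earlier years is likely but not established.

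For OAC versus no OAC the effect may be small: a shift of 0 to about 2 years between widely overlapping distributions, and a null HR of about 0.97 to 0.95 at a 1.1-year gap. For the NOAC hazard ratio it is larger, about 0.94 to 0.87 under the null at gaps of 2 to 2.8 years. All these values rest on assumed exposure trends, an assumed spread of NOAC starts and an assumed 3% to 5% yearly fall in event rates. They show the order of size and do not predict the bias.

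**What to change.** - Add calendar year of NVAF diagnosis to the propensity score model, so that it serves both matching and the overlap weights, or match within diagnosis year.
- In the NOAC comparison, use only unexposed patients diagnosed in the same calendar period as the NOAC users.
- State when observation ends. If that is also 30 June 2019, apply one diagnosis cut-off a year earlier (30 June 2018) to both groups.

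The cost is a few sentences and one variable already in the data, with somewhat fewer matches per untreated patient in some years and, if the cut-off applies, loss of the last year of entry. Numbers allow it: Feasibility counts expects around 14,000 untreated patients (12% of 120,000 = 14,400), and Sample size considerations asks for 194 unexposed. The change should be settled before matching is run.
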